### Outcome assessment

The assessment points of this study are the baseline and 3 and 12 months, at which time points the questionnaires will be sent by post to the patients with a pre-paid return envelope. At the baseline, information will be gathered on the demographics, comorbidities, work history, and previous rehabilitation measures. The primary and secondary outcomes and other measures are listed in Table 3.

**Table 3 T3:** Outcomes and other measures

**Primary outcome measure***	
Self-reported pain	WOMAC (VAS) [28-31] pain subscale
**Secondary outcome measure***	**Measurement**
Self-reported physical function, pain and stiffness	WOMAC (VAS) physical function and stiffness subscales [28-31], NPRS, mean and worst pain (past week, 3 months)
Depression, anxiety, sense of coherence, pain catastrophizing, kinesiophobia, self-efficacy, and life satisfaction	BDI-21 [34-37], BAI [38,39], 13-item SOC scale [40-46], PCS [47,48], TSK [49,50], PSEQ [51,52], 4-item LS scale [53-55]
Health-related quality of life and cost effectiveness	RAND-36 (SF-36) [56,57], 15D [58], QALY [58], OA-related sick leave, use of pain medication, knee OA-related health care visits, rehabilitation and pensions
GAC	GAC
**Other measures**	**Measurement**
Identifying risk for persistent pain	Örebro MPQ [59]
Major life events	Open question
Adherence	Attendance at meetings

*The primary end point for data analysis is 12 months. All outcome measures will be undertaken at baseline and after 3 and 12 months. WOMAC = Western Ontario and McMaster Osteoarthritis Index; NPRS = numeric pain rating scale; BDI-21 = 21-item Beck Depression Inventory; BAI = Beck Anxiety Index; SOC = sense of coherence; PCS = Pain Catastrophizing Scale; TSK = Tampa Scale for Kinesiophobia; PSEQ = Pain Self-Efficacy Questionnaire; LS = life satisfaction; RAND-36 = the RAND 36-item health survey; 15D = generic 15D instrument; QALY = quality-adjusted life years; OA = osteoarthritis; GAC = global assessment of change; MPQ = Musculoskeletal Pain Questionnaire.

The primary outcome measure of the study is the Western Ontario and McMaster Universities Osteoarthritis Index (WOMAC) self-reported pain subscale [28,29], which is to be measured with the pain subscale of the Finnish version of the WOMAC [30,31]. The Finnish WOMAC consists of three dimensions: pain (5 items), stiffness (2 items), and physical functioning (17 items). Responses for the 24 items are registered on a 0–100 mm visual analogue scale (VAS).

Secondary outcomes of the study will include WOMAC stiffness and physical function subscales [28-31], as well as numeric pain rating scales of the worst and mean pain during the previous week and past three months. The health-related quality of life will be evaluated with 15D [58] and RAND-36 [56,57]. The use of pain medication, the number of knee OA-related health care visits, sick leave days, rehabilitation and pensions will be recorded. The patients will also be asked to complete several psychological questionnaires at the assessment points: depression will be evaluated with Beck's Depression Inventory (BDI-21) [34-37], anxiety with Beck's Anxiety Index (BAI) [38,39], sense of coherence with a 13-item sense of coherence scale (SOC) [40-46], catastrophizing with the Pain Catastrophizing Scale (PCS) [47,48], kinesiophobia with Tampa Scale of Kinesiophobia (TSK) [49,50], pain self-efficacy with Pain Self-Efficacy Questionnaire (PSEQ) [51,52], and life satisfaction (LS) with a 4-item LS scale [53-55]. Finally, some questions concerning major life events and the global assessment of change will be included.

### Statistical analysis

The mean (±SD) knee joint pain score (WOMAC, VAS) was estimated by using the results of the knee joint pain scores in previous studies [60,61]. Since the knee pain has to be ≥40 mm on a 100-mm VAS (WOMAC) in this present study, we postulated that there will be a mean of at least 48±16.2 mm in the WOMAC pain subscale at baseline. In our study the 20% reduction in primary outcome (WOMAC pain) due to the intervention was considered as being clinically relevant in accordance with the OMERACT-OARSI set of responder criteria [62]. In the comparison of the mean pain scores between the groups, 54 patients per group are needed according to a power calculation with the two-tailed Student t-test with a 5% significance level and 80% power, assuming a 20% dropout rate [63].

Demographic characteristics and baseline data will be summarized by descriptive statistics. Randomly missing data in the longitudinal set-up will be imputed using expectation–maximization algorithm before the analysis in order to follow the intention to treat principle. Data on various psychological variables predicting reported knee pain will be assessed by multiple regression analysis. For outcomes measured on a continuous scale, differences between groups in the mean change from the baseline to 12 months will be evaluated using the linear mixed modeling. The model assumptions will be checked by standard diagnostic plots. The participant rating of the global assessment of change will be compared between the two groups using the two-tailed Student t-test.

Cost-effectiveness of the intervention will be evaluated by cost-utility analysis which is a techniques that incorporates the expenses of the intervention as well as the costs of the use of health care services and pain medication, sick leaves, rehabilitation and pensions. Utility analysis is based on measurement of QALY from 15D [58]. Life expectancy with 0%, 3% and 5% discounting will be incorporated in the analysis. The cost-effectiveness of the intervention can be evaluated by dividing the overall costs with the QALY.

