The patients will be randomly assigned to either the GP care and intervention group (n = 54) or the GP care control group (n = 54). Randomization will be conducted in blocks of six, separately for men and women. A computer-generated code for randomization will be constructed by a statistician who will not meet the study patients, and it will be administered via sealed opaque envelopes. The personnel responsible for data collection will be blinded to group assignment and will not be involved in providing the interventions. The code for randomization will be opened only after the statistical analyses have been performed after the 12-month follow-up point.

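### At the stated planning values, 54 per group with 20% dropout gives about 77.5% power rather than 80%: wrong as written, but a small error

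*Protocol article*

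**What the plan says.** Everything needed to check the sample size is in the Statistical analysis section of the protocol article.

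- Planning mean and SD: "a mean of at least 48±16.2 mm in the WOMAC pain subscale at baseline".
- Effect: "the 20% reduction in primary outcome (WOMAC pain) due to the intervention was considered as being clinically relevant".
- Result: "54 patients per group are needed".
- Test, error rates and attrition: "with the two-tailed Student t-test with a 5% significance level and 80% power, assuming a 20% dropout rate".

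Participants and recruitment allocates to "either the GP care and intervention group (n = 54) or the GP care control group (n = 54"), so the calculated number is also the number to be randomised, 108 in total. The article prints no difference in millimetres, no evaluable number before dropout, and no account of how dropout was added.

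**The concern.** If 54 are randomised per group and 20% are lost, the power claim has to hold with the 43 or so who remain. On the printed inputs it does not. The round result 45 × 1.2 = 54 suggests that dropout was allowed for by adding 20% of the required number. Keeping 80% of those randomised at the required level means dividing by 0.8.

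This sentence is the only justification of the sample size, and it concerns the primary outcome. As printed, a reader would credit the design with slightly more power than it has under its own dropout assumption.

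**Working it through.** **Inputs** (all from Statistical analysis unless noted)

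- Mean 48 mm, SD 16.2 mm.
- Difference between groups: 0.20 × 48 = 9.6 mm. This is derived; the article does not print it. Standardised difference: 9.6 / 16.2 = 0.593.
- Two-sided 5% (z = 1.960), 80% power (z = 0.842), equal groups (Participants and recruitment).
- Dropout 20%, stated number 54 per group.

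**Step 1. Evaluable patients needed per group**

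Normal approximation: n = 2 × [SD × (1.960 + 0.842) / difference]² = 2 × [16.2 × 2.802 / 9.6]² = 44.7, so 45.

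Two-sample t-test (noncentral t), the test that the plan names: 45.7, so 46.

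**Step 2. Reproducing the stated 54**

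| Evaluable n | × 1.2 | ÷ 0.8 |
|---|---|---|
| 45 (normal) | 54.0, so 54 | 56.25, so 57 |
| 46 (t-test) | 55.2, so 56 | 57.5, so 58 |

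Only the normal-approximation n with the 1.2 multiplier returns 54. Even without rounding before inflation, the normal figure gives 44.7 / 0.8 = 55.9, so 56.

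**Step 3. Power with the patients who remain**

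54 × 0.8 = 43.2, so about 43 per group.

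Normal approximation at 43: 9.6 / [16.2 × √(2/43)] = 2.748; 2.748 − 1.960 = 0.788; power = 78.5%.

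| Evaluable per group | t-test power | Normal power |
|---|---|---|
| 43 | 77.5% | 78.5% |
| 45 | 79.4% | 80.3% |
| 46 | 80.3% | 81.1% |
| 54 (no dropout) | 86.2% | 86.8% |

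The shortfall is 80 − 77.5 = 2.5 points by the t-test and 80 − 78.5 = 1.5 points by the normal approximation. The 1-point difference between them reflects the method and not the handling of dropout.

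**Step 4. The same gap in other terms**

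- Difference detectable with 80% power at 43 per group (t-test): 9.9 mm.
- Largest dropout that keeps 80% power for 9.6 mm: 1 − 46/54 = 14.8% (t-test), or 1 − 45/54 = 16.7% (normal).
- Number to randomise for 80% power after 20% dropout: 58 per group, 116 in total (t-test), or 57 per group, 114 in total (normal), against 108.

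**Step 5. Sensitivity to the mean**

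The effect is a percentage, so it grows with the mean. With SD held at 16.2 mm (an assumption), 43 per group reaches 80% power at a mean of 9.9 / 0.20 = 49.5 mm by the t-test, or about 48.9 mm by the normal approximation. At a mean of 50 mm the difference is 10 mm, the t-test needs 43, and 43 / 0.8 = 53.75, so 54.

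**The case against.** **The mean is given as a floor.** The article says at least 48 mm, and 1.0 to 1.5 mm above that the stated 54 is correct. This stands as a limit on the claim: a reader might infer that 54 per group, 80% power and 20% dropout can never hold together, and that goes too far. It does not remove the point. No other planning mean is given, and a number justified by a lower bound should hold at that bound.

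**The cause is not printed.** A reader might infer that the multiplication by 1.2 is established and explains the whole shortfall. The article supports neither. It shows no inflation step, the match to 54 works only from the normal-approximation 45, and about 1 of the 2.5 points is t-test versus normal. The shortfall itself does not depend on the cause.

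**The planned analysis is a linear mixed model, not a t-test.** If that model adjusted for baseline (an assumption, not stated), power at 43 per group would be about 81% at a baseline to 12-month correlation of 0.3, and about 88% at 0.5. For an unadjusted change score it would be unchanged at 0.5 and lower below that. So actual power may well exceed 80%. The sample-size sentence, however, rests on a t-test of mean scores and claims no such gain.

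**Missing data will be imputed.** Imputation by expectation-maximisation does not restore the information lost with dropouts, and the plan itself budgets for dropout in the sample size.

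**The gap is small.** This stands. It amounts to 2 to 3 evaluable patients per group, or 0.3 mm in detectable difference on a 100-mm scale. The mean and SD were themselves estimated from previous studies and are uncertain.

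**Conclusion.** The statement is wrong as written, and the error is minor. At a mean of 48 mm, a 20% reduction (9.6 mm), SD 16.2 mm and a two-tailed 5% t-test, 54 per group with 20% dropout gives about 77.5% power (78.5% by the normal approximation). Neither method delivers the stated 80%.

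The multiplier of 1.2 is the likely explanation but remains an inference. A reader might also conclude that the trial is materially underpowered or must recruit more patients. A deficit of 1.5 to 2.5 points that disappears at a mean of about 49 to 49.5 mm does not support that, and a null result would in any case be read mainly from its confidence interval.

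The conclusion rests on taking 48 mm as the planning mean and on reading the 20% as a between-group difference, which the wording about a reduction due to the intervention supports.

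**What to change.** Keep 108 patients and correct the sample-size sentence in Statistical analysis. Any one of these would do:

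- *54 patients per group give about 77.5% power (two-sided 5% t-test) for a 9.6 mm difference with SD 16.2 mm after 20% dropout.*
- *After 20% dropout, 54 patients per group give 80% power for a 9.9 mm difference with SD 16.2 mm.*
- *54 patients per group give 80% power for a 9.6 mm difference with SD 16.2 mm if dropout is at most about 15%.*

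If the calculation in fact used a different mean or difference, print that value instead.

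The cost is one sentence of wording and, unless a different input is disclosed, a slightly less favourable figure. Recruitment, randomisation and analysis do not change.

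### EM imputation before the mixed model, with no stated allowance for imputation error, overstates precision at 12 months if arm is in the imputation and shrinks the effect if it is not

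*Protocol article*

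**What the plan says.** Under Statistical analysis the protocol article gives its rule for missing data in one sentence: randomly missing longitudinal data "will be imputed using expectation–maximization algorithm before the analysis in order to follow the intention to treat principle". For continuous outcomes it then says that "differences between groups in the mean change from the baseline to 12 months will be evaluated using the linear mixed modeling". The imputation therefore comes first and the mixed model is fitted to the completed data.

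The footnote to Table 3 makes this the primary analysis: "The primary end point for data analysis is 12 months". It also fixes three measurement occasions: "All outcome measures will be undertaken at baseline and after 3 and 12 months".

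The sample-size paragraph supplies the planning figures: "a mean of at least 48±16.2 mm in the WOMAC pain subscale at baseline", a relevant effect described as "the 20% reduction in primary outcome (WOMAC pain) due to the intervention was considered as being clinically relevant", and a "two-tailed Student t-test with a 5% significance level and 80% power, assuming a 20% dropout rate".

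The article does not give the number of completed data sets, say whether random error is added to the filled-in values, mention any correction of the variance, or say whether treatment arm enters the imputation model.

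**The concern.** EM imputation in its usual form replaces a missing score by its expected value given the patient's other scores. Such values lie exactly on the fitted line and carry no residual scatter. A mixed model fitted afterwards cannot tell them from real measurements, so it counts information that was never collected.

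The consequence depends on the imputation model:

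- **Arm included.** The estimate is unbiased under the stated missingness, but its standard error is too small and the test rejects too often.
- **Arm left out.** Patients with missing scores are filled in from a line common to both arms. The arms are pulled together and the effect is understated.

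The reason given for the step also fails. A likelihood-based mixed model already uses every observed visit of every randomised patient, and it is valid under the same random-missingness assumption. What is at stake is the primary outcome at the primary time point.

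**Working it through.** **Inputs from the article.** Mean 48 mm, SD 16.2 mm, 20% relative effect, two-sided 5% level, 80% power, 20% dropout, 54 per group, visits at baseline, 3 and 12 months.

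**Reproducing the plan's figure.** Effect = 0.20 × 48 = 9.6 mm. Normal approximation: n per group = 2 × (1.960 + 0.842)² × 16.2² / 9.6² = 2 × 7.85 × 262.44 / 92.16 = 44.7, so 45. Then 45 × 1.2 = 54, the stated number. This confirms that 9.6 mm and 16.2 mm are the planning values. (Dividing by 0.8 would give 57; that is a separate matter.)

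**Assumptions not in the article.** Equal correlation between visits of 0.3, 0.5 or 0.7; SD 16.2 at every visit; the effect present at both 3 and 12 months; data missing completely at random, with 20% missing at 12 months and half of those also missing at 3 months; a random-intercept mixed model with arm-by-visit terms, fitted by REML.

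**Rough check by hand.**
- Arm included: about 0.8 × 54 = 43.2 patients per arm have a 12-month score, but the model counts 54. The count alone shrinks the standard error by a factor of √(43.2/54) = 0.89, and the missing scatter shrinks it further.
- Arm left out: if filled-in patients contributed no arm difference at all, the estimate would be 0.8 × 9.6 = 7.68 mm. Observed 3-month scores recover a little of the rest.

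**Simulation.** 1,200 runs with no effect and 600 with a 9.6 mm effect at each correlation.

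| Correlation | Analysis | True SE (no effect) | Reported SE | Ratio | Type I error | Mean estimate for true 9.6 mm |
|---|---|---|---|---|---|---|
| 0.3 | EM with arm | 3.87 | 3.46 | 0.89 | 8.0% | 9.45 |
| 0.3 | EM without arm | 3.36 | 3.46 | 1.03 | 5.0% | 7.83 |
| 0.3 | Observed data only | 3.88 | 3.96 | 1.02 | 5.0% | 9.45 |
| 0.5 | EM with arm | 3.41 | 2.91 | 0.85 | 9.2% | 9.66 |
| 0.5 | EM without arm | 2.91 | 2.91 | 1.00 | 4.2% | 8.12 |
| 0.5 | Observed data only | 3.41 | 3.38 | 0.99 | 4.4% | 9.66 |
| 0.7 | EM with arm | 2.57 | 2.25 | 0.88 | 7.9% | 9.60 |
| 0.7 | EM without arm | 2.17 | 2.25 | 1.04 | 3.9% | 8.13 |
| 0.7 | Observed data only | 2.56 | 2.64 | 1.03 | 4.3% | 9.60 |

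The Monte Carlo standard error of a 5% rate over 1,200 runs is √(0.05 × 0.95 / 1200) = 0.6 percentage points, so 7.9% to 9.2% is clearly above 5%.

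With arm included, EM leaves the true standard error where it was without imputation (3.87 against 3.88, 3.41 against 3.41, 2.57 against 2.56). Only the reported one falls. The step buys no precision.

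Without arm, the shrinkage is (9.60 − 8.13)/9.60 = 15% to (9.60 − 7.83)/9.60 = 18%. Power at the three correlations is 63%, 79% and 97%, against 67%, 80% and 97% from observed data.

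**Sensitivity, using a 12-month change-score test instead of the mixed model.**
- If every dropout also misses 3 months: type I error 9.4% to 10.9% with arm; estimates of 7.5 to 7.6 mm without arm.
- With half of dropouts also missing 3 months and arm included: type I error 9% to 11% at 20% missing, 6% to 7% at 10% missing, and about 5.4% at 5% missing (the last at correlation 0.3 only).

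**The case against.** Several points on the other side have weight.

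**The article is a condensed plan.** Imputation detail may sit in an analysis plan that is not shown. That would answer a complaint about missing detail. It does not answer this one: the article names the method, places it before the analysis and gives the reason. Because it comes before the analysis, EM cannot be read as merely the fitting algorithm of the mixed model.

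**A single fill-in is an inference.** This stands. The number of data sets is not given. One filled-in data set is the natural reading, but it remains a reading.

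**The size depends on how much is missing.** This also stands. The 20% is a planning allowance, and with good retention the inflation is small.

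A reader might also infer more than the article supports:

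- *That blinding makes an imputation pooled over arms likely.* The article opens the randomisation code only after the analyses, yet those analyses compare the groups, so a masked group label must be available. It can enter an imputation model just as it enters the mixed model. Omitting arm is an open possibility, no more.
- *That the primary test suffers both an inflated error rate and a diluted effect.* They are alternatives. Without arm, type I error is 3.9% to 5.0% and little power is lost; the harm is a biased estimate.
- *That EM can simply be struck out.* It is the only stated handling of missing data. A visit-level mixed model does not deal with a missing item among the five WOMAC pain items, nor does it cover the t-test of the global assessment of change or the regression on psychological predictors.

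**Conclusion.** The point holds. Followed as written and read in the natural way, the plan puts an avoidable error into the primary 12-month analysis. With arm in the imputation, the false-positive rate is about 8% to 9%. Without arm, an effect equal to the plan's own threshold of clinical relevance would be reported 15% to 18% too small. The article does not say which applies, and neither is acceptable when the same mixed model on observed data showed neither fault (type I error 4.3% to 5.0%, mean estimate 9.45 to 9.66 mm).

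The sizes rest on the assumed correlations, dropout pattern and random-intercept structure, and on 20% being missing at 12 months. The direction did not change over the range tried.

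**What to change.** Before the data are analysed, replace the imputation sentence with three rules:

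1. **Missing visits, continuous outcomes.** No imputation. Fit the linear mixed model by REML to all observed scores of all randomised patients, in their allocated arms. This follows intention to treat under the missing-at-random assumption that the plan already makes.
2. **Missing items within a returned questionnaire.** Apply the instrument's own scoring rule, and name that rule.
3. **Analyses that need complete data** (QALY and costs, the comparison of the global assessment of change, the predictor regression). Use multiple imputation with arm in the imputation model, combined by Rubin's rules.

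The cost is a few sentences, and for the primary analysis less work than now planned. Confidence intervals become wider: in the simulation the reported standard error rises from 3.46 to 3.96, from 2.91 to 3.38 and from 2.25 to 2.64 mm, or 14% to 17%. That is the uncertainty the data actually carry.

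### The trial is sized on pain scores but analysed on change from baseline, and the plan does not state adjustment for baseline pain or sex; stating it would be at least as precise and costs nothing.

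*Protocol article*

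**What the plan says.** The Statistical analysis section of the protocol article uses two different quantities for the same primary question.

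- **Sample size.** The calculation concerns scores: "In the comparison of the mean pain scores between the groups, 54 patients per group are needed". It is a "power calculation with the two-tailed Student t-test with a 5% significance level and 80% power", "assuming a 20% dropout rate". The variability comes from a single time point: "we postulated that there will be a mean of at least 48±16.2 mm in the WOMAC pain subscale at baseline". The target is relative: "the 20% reduction in primary outcome (WOMAC pain) due to the intervention was considered as being clinically relevant".
- **Analysis.** For continuous outcomes, "differences between groups in the mean change from the baseline to 12 months will be evaluated using the linear mixed modeling". Table 3 names the WOMAC pain subscale as primary, sets 12 months as the primary end point, and has the outcomes measured at baseline, 3 and 12 months.
- **Randomisation.** Under Participants and recruitment: "Randomization will be conducted in blocks of six, separately for men and women".

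The article gives no SD of change and no correlation between baseline and 12-month pain. For the mixed model it names no covariates, neither including nor excluding baseline pain or sex, and it does not say how the baseline value enters.

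**The concern.** In its ordinary form, a mixed model for a group difference in change keeps baseline in the outcome vector, fits group-by-time, and leaves the baseline means free in each arm. With complete data it then returns the simple difference in mean change. That contrast carries the noise of the baseline measurement as well as that of the follow-up. Randomisation already makes the true baseline means equal, so estimating them separately by arm gains nothing.

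Two things are at stake. The stated 80% power belongs to a different contrast from the one to be reported. The primary estimate may also be less precise than the data allow, in a trial with little slack. Sex raises a smaller point of the same kind: it restricts the randomisation, and leaving it out of the model tends to overstate the standard error if sex predicts pain.

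**Working it through.** **Inputs.** From the Statistical analysis section: baseline mean 48 mm, SD 16.2 mm, 20% reduction, two-sided 5%, 80% power, 20% dropout. From Participants and recruitment: 54 per arm. Assumed: the 12-month SD (taken as 16.2 mm) and the correlation r, neither of which the article gives.

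**Step 1: reproduce the plan's figure.** The difference is 0.20 × 48 = 9.6 mm, and the standardised difference is 9.6/16.2 = 0.593. The normal approximation gives n = 2 × (1.960 + 0.842)² × (16.2/9.6)² = 44.7, so 45 per arm. Then 45 × 1.2 = 54, the stated figure. It is therefore a comparison of scores at one time point, with no baseline-outcome correlation used. With 20% lost, 54 × 0.8 ≈ 43 per arm remain, and the score comparison has 78% power.

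**Step 2: variances under equal SDs (s = 16.2 mm).**

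- Score alone: s².
- Unadjusted change: 2(1 − r)s².
- Baseline-adjusted: (1 − r²)s².

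The ratio of adjusted to change variance is (1 + r)/2, which is below 1 for any r below 1. The ratio of change to score variance is 2(1 − r), which exceeds 1 only when r < 0.5.

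**Step 3: power with 43 per arm** (t-test, 9.6 mm):

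| r | SD of change (mm) | adjusted SD (mm) | power, change | power, adjusted | variance ratio, adjusted/change |
|---|---|---|---|---|---|
| 0.2 | 20.49 | 15.87 | 57% | 79% | 0.60 |
| 0.3 | 19.17 | 15.45 | 63% | 81% | 0.65 |
| 0.4 | 17.75 | 14.85 | 70% | 84% | 0.70 |
| 0.5 | 16.20 | 14.03 | 78% | 88% | 0.75 |
| 0.6 | 14.49 | 12.96 | 86% | 92% | 0.80 |
| 0.7 | 12.55 | 11.57 | 94% | 97% | 0.85 |

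The score comparison stays at 78% in every row.

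**Step 4: unequal SDs.** Write s0 for the baseline SD and s1 for the 12-month SD. Var(change) = s0² + s1² − 2·r·s0·s1 and Var(adjusted) = (1 − r²)s1². The difference is (s0 − r·s1)², which is never negative, so the direction does not depend on equal SDs. The size does. With s1 = 16.2 mm and r = 0.3, Var(adjusted) = 0.91 × 262.4 = 238.8, and power is 81% throughout:

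| s0 (mm) | Var(change) | power, change | variance ratio, adjusted/change |
|---|---|---|---|
| 16.2 | 367.4 | 63% | 0.65 |
| 12 | 289.8 | 73% | 0.82 |
| 10 | 265.2 | 77% | 0.90 |
| 8 | 248.7 | 80% | 0.96 |

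Change and score comparisons then have equal variance at r = s0/(2·s1), which is 0.5 only when the SDs are equal.

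**Step 5: bias.** In 20,000 simulated trials per setting, with 43 per arm, all three contrasts averaged within 0.04 mm of the true 9.6 mm. Their standard errors in mm, for change, adjusted and score, were 4.13, 3.35, 3.48 at r = 0.3; 3.52, 3.05, 3.49 at r = 0.5; and 2.70, 2.50, 3.49 at r = 0.7.

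**The case against.** The strongest reply is that the article names no covariates at all. It condenses a fuller plan, and covariate lists are commonly left to that plan. The quoted wording also fits an efficient analysis: change as outcome with baseline as covariate gives the same treatment effect as adjusted scores, and a model with a common baseline mean also estimates a difference in change. This stands. A reader might infer that the plan rules out conditioning on baseline pain or sex; the article does not say so.

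A reader might also infer that analysing change loses precision whatever the data look like. That is not supported either. Against the score comparison that was powered, change gains when r exceeds 0.5 under equal SDs (86% at 0.6 and 94% at 0.7, against 78%). The 40 mm entry threshold may lower r, but it may also shrink the baseline SD, and Step 4 shows that this narrows the gap. One cannot invoke the first effect and ignore the second.

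Finally, sizing with a simple t-test and analysing with a mixed model is common, and the issue is efficiency, not validity. That is fair. It does not remove the mismatch: the article states a power calculation for one contrast and an analysis of another, with nothing to connect them.

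**Conclusion.** The point holds as one of precision and coherence. The sample size rests on scores, the analysis is stated for change, and adjustment for baseline pain or sex is not stated. If the model is run with baseline means free by arm, it is unbiased but never more precise than the baseline-adjusted analysis, apart from one degree of freedom.

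Under equal SDs of 16.2 mm and 43 completers per arm, the shortfall in power is about 18 percentage points at r = 0.3, 10 at r = 0.5 and 3 at r = 0.7. At r = 0.3 with a baseline SD of 10 mm it is about 4 points. The direction is certain; the size depends on r and on the two SDs, of which the article gives only a postulated baseline SD. The gain from adjusting for sex cannot be computed, because no sex effect is given.

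**What to change.** State the primary model: a linear mixed model of the 3- and 12-month WOMAC pain scores, with baseline WOMAC pain (by time), sex, group, time and group-by-time, and the 12-month group contrast as primary. An equivalent choice for the baseline adjustment is to keep baseline in the outcome vector and constrain the arm means to be equal there, again with sex in the model. Use the same form for the continuous secondary outcomes, each with its own baseline. Restate power for this model, giving the assumed correlation and 12-month SD and a range around them.

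This costs wording only. Baseline pain is collected from all participants and sex is known at randomisation, so no extra data or patients are needed. If the full plan already specifies such a model, one sentence saying so and a matching power statement are enough. It should be fixed before the 12-month data are analysed, so that no choice between adjusted and unadjusted results is left open.

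### The cost-utility analysis brings in life expectancy although 15D and resource use are observed only to 12 months, so its result would rest on persistence that the trial does not observe and that varying the discount rate does not test

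*Protocol article*

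**What the plan says.** The economic evaluation is in the last paragraph of the Statistical analysis section of the protocol article. It is a cost-utility analysis with QALYs derived from the 15D. On the time horizon it says: "Life expectancy with 0%, 3% and 5% discounting will be incorporated in the analysis". On costs, it says that the technique "incorporates the expenses of the intervention as well as the costs of the use of health care services and pain medication, sick leaves, rehabilitation and", as the last component, pensions. The summary measure is then described: "The cost-effectiveness of the intervention can be evaluated by dividing the overall costs with the QALY".

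The observation period is set elsewhere. The Outcome assessment section says: "The assessment points of this study are the baseline and 3 and 12 months". The footnote to Table 3 adds "All outcome measures will be undertaken at baseline and after 3 and 12 months" and "The primary end point for data analysis is 12 months". The 15D, QALYs, sick leave, medication, health care visits, rehabilitation and pensions are all listed in that table as secondary outcomes. The Design section gives the intervention as six weeks long. No later assessment is planned.

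**The concern.** Discounting has a material effect only beyond the first year. A plan that brings in life expectancy at 0%, 3% and 5% has therefore chosen a horizon longer than its follow-up. Every QALY after month 12 comes from an assumption about how long the effect of a six-week program lasts, and the article states no such assumption. The only variation it plans is in the discount rate, which rescales the projected QALYs but leaves persistence untested.

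The article's own text gives reason for caution. The Background reports a 10-week group program on similar principles in 40 osteoarthritis patients, with no long-term difference from an education control. The longer-term benefits it cites for the present model were seen in back and neck pain. The Design section calls the study open, the 15D is self-reported, and the Discussion regards an attention effect as probable. Any such component of the 15D difference would be projected along with the true effect.

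The Discussion hopes that the cost-effectiveness results will support inclusion in care recommendations. A ratio determined mainly by an untested assumption would be a weak basis for that.

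**Working it through.** The article gives no QALY, cost, life-expectancy or cost-per-QALY figure, so there is nothing to reproduce. The check is how far the ratio moves under different ways of bringing in life expectancy. The ratio is treated as incremental (difference in costs over difference in QALYs).

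**Inputs from the article.** Discount rates r of 0%, 3% and 5% (Statistical analysis); 15D at 0, 3 and 12 months (Outcome assessment, Table 3); ages 35 to 75 (Table 1).

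**Assumptions, not in the article.** Remaining years L of 10, 20 or 45; a 15D gain of 0.02 at both 3 and 12 months; an extra first-year cost of 500 units.

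**1. Constant difference carried for L years.** The multiplier on a one-year difference is A(L, r) = Σ 1/(1+r)^t for t = 0 to L−1.

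| L | 0% | 3% | 5% |
|---|---|---|---|
| 1 | 1.0 | 1.0 | 1.0 |
| 10 | 10.0 | 8.8 | 8.1 |
| 20 | 20.0 | 15.3 | 13.1 |
| 45 | 45.0 | 25.3 | 18.7 |

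With L = 1, the within-trial horizon, the discount rate has no effect. With only 12-month costs in the numerator, cost per QALY falls by the factor in the table.

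**2. Effect halving each year.** The multiplier is Σ 0.5^t/(1+r)^t. This gives 2.0, 1.94 and 1.91 at 0%, 3% and 5%, and is the same to two decimals for every L from 10 to 45.

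**3. Illustration with L = 20.**

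- Within-trial area under the curve: 0.25 × (0 + 0.02)/2 + 0.75 × (0.02 + 0.02)/2 = 0.0025 + 0.0150 = 0.0175 QALY. Ratio: 500/0.0175 = 28,571 per QALY.
- Constant gain for life, 12-month costs only: 0.02 × A = 0.400, 0.306 and 0.262 QALY. Ratios: 1,250, 1,631 and 1,911 per QALY.
- Constant gain for life, extra cost of 100 in each later year: (500 + 100 × (A − 1))/(0.02 × A) = 6,000, 6,305 and 6,528 per QALY.
- Constant gain for life, the full 500 in every year: (500 × A)/(0.02 × A) = 25,000 per QALY at every rate.

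Against the area-under-the-curve comparator, the drop in the second line is 28,571/1,250 = 22.9-fold at 0% and 28,571/1,911 = 15.0-fold at 5%. That exceeds the 20.0 and 13.1 in the table because the area under the curve allows for the rise from zero over the first 3 months.

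**4. Dependence on the 12-month value.** With a gain of 0.02 at 3 months and none at 12 months, the within-trial QALY gain is 0.25 × 0.01 + 0.75 × 0.01 = 0.0100, but carrying the 12-month value forward adds nothing. With the pattern reversed, the within-trial gain is 0.25 × 0 + 0.75 × 0.01 = 0.0075, but the projection at 0% is again 0.400. The projection is thus governed by one time point and the persistence rule.

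**The case against.** A reader might infer that the plan credits a one-year 15D difference unchanged until death, sets it against 12 months of costs, and so produces a cost per QALY that is far too low. The article does not say this. It says that life expectancy will be incorporated, without saying how. It states no duration or waning of the effect. It gives no horizon for costs, refers to them as overall costs, and includes pensions, which can run for years. 15D and resource use are recorded on the same schedule, so nothing in the text shows that one is projected and the other is not.

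The direction of any bias is not fixed either. The Background cites lower long-term health and social care costs after a related rehabilitation program. If savings occurred here and persisted, leaving out later costs would work against the intervention, and a ratio with a negative cost difference has no simple meaning.

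It is also fair to say that a condensed article can leave the waning rule, the cost projection and the exact QALY calculation to a fuller plan, that projecting beyond follow-up is not an error in itself, and that this is a secondary analysis.

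These points stand, and they make the size and direction conditional. They do not remove the concern. The life-expectancy horizon is a stated choice, not an omission; the article names no within-trial analysis beside it; and no fuller plan could make 12 months of data observe a longer effect.

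**Conclusion.** The point holds in conditional form. The stated horizon goes beyond the observed 12 months, so the cost-utility result would rest on unobserved persistence, which the three discount rates do not probe.

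The possible effect on cost per QALY ranges widely:

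- a fall of about 8- to 20-fold if the difference is held constant for an assumed 10 to 20 years and only 12-month costs count, and up to 45-fold at 0% if 45 years are assumed for the youngest patients;
- a factor of about 2 if the effect halves yearly and only 12-month costs count;
- little change (25,000 against 28,571 in the illustration) if the full extra cost is carried over the same horizon.

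Remaining years, the 15D gain and the costs are all assumed. That spread is the finding: assumptions the article does not state, rather than trial data, would decide the answer. The primary WOMAC pain comparison and the sample size are unaffected. This is a cheap improvement.

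**What to change.** Make the base case within-trial. Calculate 12-month QALYs for each patient as the area under the 15D curve at 0, 3 and 12 months, and estimate the difference between groups adjusted for baseline 15D. Set it against the difference in 12-month costs and report the incremental ratio, undiscounted.

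Keep any life-expectancy projection as a labelled scenario. State how the effect is assumed to wane, project costs over the same horizon as QALYs, and vary the persistence assumption as well as the discount rate.

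The cost is a change of wording in the Statistical analysis section and one further analysis on data already being collected. The drawback is that the reported cost per QALY may be less favourable than under a lifetime horizon.
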